# Abbreviation

| Abbreviation | Full term                                 |
|--------------|-------------------------------------------|
| ADR          | Adverse drug reaction                     |
| AE           | Adverse event                             |
| CRF          | Case report form                          |
| EC           | Ethics committee                          |
| EDC          | Electronic data capture                   |
| GCP          | Good clinical practice                    |
| IRB          | Institutional review board                |
| ITT          | Intention-to-treat                        |
| LDHR         | Lumbar disc herniation with radiculopathy |
| LMM          | Linear mixed model                        |
| LOPM         | Lumbar oblique pull manipulation          |
| MCID         | Minimal clinically important difference   |
| NSAIDs       | Non-steroidal anti-inflammatory drugs     |
| ODI          | Oswestry Disability Index                 |
| PI           | Principal investigator                    |
| PP           | Per-protocol                              |
| QC           | Quality control                           |
| RCT          | Randomized controlled trial               |
| SAE          | Serious adverse event                     |
| SF-12        | 12-Item Short Form Health Survey          |
| SR           | Sustained release                         |
| TCM          | Traditional Chinese medicine              |
| VAS          | Visual analog scale                       |
| YBT          | Yaobitong                                 |

## Summary

|                                         |                                                                                                                                                                                                                                                                                                                                                                                                                                                                                                                                                                                                                                                                                                                                                                                                                                                                                                                                                                                                                                                                                                                                                                                                                                                                                                                                                                                                                                                                                                                                                                                                                                                                                                                                                                                               |
|-----------------------------------------|-----------------------------------------------------------------------------------------------------------------------------------------------------------------------------------------------------------------------------------------------------------------------------------------------------------------------------------------------------------------------------------------------------------------------------------------------------------------------------------------------------------------------------------------------------------------------------------------------------------------------------------------------------------------------------------------------------------------------------------------------------------------------------------------------------------------------------------------------------------------------------------------------------------------------------------------------------------------------------------------------------------------------------------------------------------------------------------------------------------------------------------------------------------------------------------------------------------------------------------------------------------------------------------------------------------------------------------------------------------------------------------------------------------------------------------------------------------------------------------------------------------------------------------------------------------------------------------------------------------------------------------------------------------------------------------------------------------------------------------------------------------------------------------------------|
| Title                            | Clinical Evaluation of TCM Regimens for Lumbar Disc Herniation with Radiculopathy.                                                                                                                                                                                                                                                                                                                                                                                                                                                                                                                                                                                                                                                                                                                                                                                                                                                                                                                                                                                                                                                                                                                                                                                                                                                                                                                                                                                                                                                                                                                                                                                                                                                                                                            |
| Objective                        | To evaluate the therapeutic effect in combination of Yaobitong (YBT) and lumbar oblique pull manipulation (LOPM) for Lumbar disc herniation with radiculopathy (LDHR) patients with moderate pain.                                                                                                                                                                                                                                                                                                                                                                                                                                                                                                                                                                                                                                                                                                                                                                                                                                                                                                                                                                                                                                                                                                                                                                                                                                                                                                                                                                                                                                                                                                                                                                                            |
| Study design                     | Multicenter, randomized, three-arm, parallel-group controlled trial.                                                                                                                                                                                                                                                                                                                                                                                                                                                                                                                                                                                                                                                                                                                                                                                                                                                                                                                                                                                                                                                                                                                                                                                                                                                                                                                                                                                                                                                                                                                                                                                                                                                                                                                          |
| Inclusion and exclusion criteria | 
Inclusion Criteria:
 
 
1. Confirmed diagnosis of LDHR.
 
2. Aged 18–65 years (inclusive).
 
3. Moderate low back or leg pain intensity assessed by visual analog scale (VAS): <math>\geq 4</math> and <math>< 7</math>.
 
 
Exclusion Criteria:
 
 
1. History of spinal surgery.
 
2. Spinal compression fractures; lumbar spondylolisthesis grade II or higher; lumbar spondylolysis; lumbar spinal stenosis.
 
3. Spinal tumors; spinal tuberculosis; severe osteoporosis (T-score <math>\leq -3.0</math> or associated osteoporotic fractures); diabetes with peripheral neuropathy.
 
4. Known allergy or hypersensitivity to non-steroidal anti-inflammatory drugs (NSAIDs), Chinese herbal medicines, or other related medications.
 
5. History of gastrointestinal ulcer or bleeding.
 
6. Recent coronary artery bypass graft surgery; current use of dual antiplatelet therapy; presence of coagulation disorders or high risk of bleeding.
 
7. Severe skin diseases or skin lesions in the lumbar region.
 
8. Pregnancy or breastfeeding.
 
9. Severe heart failure, stroke, or other major cardiovascular or cerebrovascular diseases; severe hepatic or renal dysfunction.
 
10. Cauda equina syndrome; lower limb muscle strength of grade 3 or less (on a 0-5 scale); or persistent loss of motor/sensory function with clear indications for surgical intervention.
 
11. Inability to provide informed consent or comply with study procedures (e.g., significant visual, hearing, or speech impairment; intellectual disability; or severe mental disorder).
 
 |
| Endpoints                        | Efficacy measures will be recorded at baseline and 3 days, 1 week, 2 weeks, 6 weeks, 14 weeks, and 26 weeks after randomization. The measurement instruments will be Oswestry Disability Index (ODI) for the functional disability, VAS for the leg and low back pain, and 12-Item Short Form Health Survey (SF-12) for the quality of life. Blood routine tests and liver and kidney function tests will be conducted before randomization and at 2 weeks after randomization. In addition, detailed records of each patient's gastrointestinal discomfort, skin allergies, and other adverse events will be collected at 2 weeks after randomization to assess safety. At the 26-week post-randomization follow-up, a repeat MRI will be performed. The change in the sagittal area of the disc herniation from baseline to 26 weeks will be measured, with a reduction of $\geq 40\%$ defined as the occurrence of disc resorption. The disc resorption rates will be calculated. The primary outcome will be change in ODI from baseline to week 2. The minimal clinically important difference (MCID) for ODI will be set at $\geq 7$ points, consistent with prior studies. Secondary outcomes will include leg and low back pain VAS, SF-12, adverse events, and disc resorption rates.                                                                                                                                                                                                                                                                                                                                                                                                                                                                                                |

**The National Key Research and Development Program of China, No. 2021YFC1712802**

|                             |                                                                                                                                                                                                                                                                                                                      |
|-----------------------------|----------------------------------------------------------------------------------------------------------------------------------------------------------------------------------------------------------------------------------------------------------------------------------------------------------------------|
| Safety indicators    | Blood routine tests and liver and kidney function tests will be conducted at baseline (before randomization) and at 2 weeks after randomization. Additionally, detailed records of gastrointestinal discomfort, skin allergies, and other adverse events will be collected at the 2-week follow-up to assess safety. |
| Sample size          | A total of 438 LDHR patients with moderate pain will be included.                                                                                                                                                                                                                                                    |
| Intervention         | Participants were randomly assigned in a 1:1:1 ratio to one of three treatment groups: (1) The YBT group: YBT capsules were administered orally. (2) The LOPM group: LOPM was performed. (3) The YBT + LOPM group: Participants received both YBT and LOPM.                                                          |
| Study duration       | 2-week treatment and 24-week follow-up.                                                                                                                                                                                                                                                                              |
| Statistical unit     | Institute of Basic Research in Clinical Medicine, China Academy of Chinese Medical Sciences.                                                                                                                                                                                                                         |
| Expected progression | The trial will commence patient enrollment in January 2023, with complete enrollment and follow-up anticipated by December 2024. Data compilation and statistical analysis are projected to be completed by April 2025.                                                                                              |

## Study protocol

### 1. Background

Globally, low back pain represents a paramount burden to public health, ranking as the leading cause of productivity loss and the foremost contributor to years lived with disability in high- and middle-income nations. Lumbar disc herniation with radiculopathy (LDHR) is one of the most common causes of low back pain. It is roughly estimated that around 1%-3% of the population suffer from LDHR annually. Alarming, the trend is worsening due to an aging population and evolving lifestyles, with LDHR now affecting younger individuals at an increasing rate. This escalating prevalence underscores the critical need for effective prevention and management strategies to alleviate the substantial burden on patients and healthcare systems.

Treatment options for LDHR include both surgical and non-surgical approaches, with the choice primarily dependent on symptom severity. In certain clinical scenarios, such as cauda equina syndrome, immediate surgical intervention is mandatory. While surgery is effective, it is associated with substantial costs and potential risks. Non-surgical management is considered the first-line option for the majority, particularly during the initial 6-week treatment period, especially for those presenting with moderate pain.

For LDHR, Traditional Chinese Medicine (TCM) modalities, notably Chinese patent medicine and manual therapy have shown potential in improving patients' quality of life, alleviating discomfort, and restoring motor function, with a favorable safety profile. Yaobitong (YBT) capsule, a Chinese patent medicine approved by the National Medical Products Administration (NMPA) for treating LDHR, is widely used in orthopedic clinical practice in China. Similarly, lumbar oblique pull manipulation (LOPM) is a characteristic manual therapy technique extensively employed in Chinese orthopedic and rehabilitation settings.

In recent years, a growing body of research has suggested that combining internal and external therapies may produce synergistic effects in the management of musculoskeletal disorders. However, despite the widespread combined use of YBT and LOPM for LDHR in Chinese clinical practice, no randomized controlled trial systematically evaluated the efficacy of this combination therapy.

Therefore, focusing on LDHR patients with moderate pain, we will conduct a multicenter, randomized, three-arm parallel-group controlled trial to evaluate the efficacy and safety of combination of YBT and LOPM.

### 2. Objective

To evaluate the therapeutic effect in combination of YBT and LOPM for LDHR patients with moderate pain.

### 3. Study design

This is a multicenter, randomized, three-arm, parallel-group controlled trial that will be conducted at 13 tertiary hospitals in China.

### **3.1. Randomization and Masking**

An independent third party, the Institute of Basic Research in Clinical Medicine at the China Academy of Chinese Medical Sciences, will generate the randomization sequence and oversee the masking procedures. A stratified block randomization method will be employed, using study center as stratification factors. Random sequences with a block size of 6 will be generated using SAS, version 9.4 (SAS Institute). Allocation concealment will be ensured through a password-protected, central online randomization system. Investigators will be able to access the treatment assignment only after a patient has completed eligibility confirmation and has provided written informed consent.

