## **5. Treatment**

### **5.1. Treatment protocol**

Participants will be randomly assigned in a 1:1:1 ratio to one of three treatment groups: (1) The YBT group: YBT capsules will be administered orally. (2) The LOPM group: LOPM will be performed. (3) The YBT + LOPM group: Participants will receive both YBT capsules and LOPM. In addition to their assigned treatments, all participants will perform standardized lumbar functional exercises throughout the treatment period.

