### **10.6 Statistical method**

The primary efficacy analysis will follow the intention-to-treat (ITT) principle, including all randomly assigned patients. All analyses will be performed using R software, version 4.4.0 (R Foundation for Statistical Computing). Missing data for the longitudinal outcomes will be handled under the assumption of missing at random using multiple imputation. Imputation will be performed using the Multivariate Imputation by Chained Equations (MICE) package in R, generating 5 imputed datasets. The imputation model will include all longitudinal outcome measures from all-time points and all baseline covariates listed above. Results from the imputed datasets will be pooled according to Rubin's rules. Baseline characteristics will be summarized using descriptive statistics. For the continuous outcomes, between-group differences at each specific time point and within-group changes from baseline will be evaluated via pairwise comparisons of the estimated marginal means derived from the linear mixed model (LMM), which will be fitted using the lme4 package (version 1.1.35). These comparisons will be conducted using the emmeans package (version 1.10.0) with Tukey's method for adjustment of P values to control the

family-wise error rate. The model will include fixed effects for treatment group, time (modeled as a categorical factor), and their interaction. The model will be adjusted for the following prespecified baseline covariates: sex, age, body mass index, total duration of lumbar disc disease, duration of the current progressive episode, and degree of herniation at the symptomatic disc level. For categorical outcomes, between-group comparisons will be performed using the chi-square test or Fisher's exact test as appropriate, while the Bonferroni correction will be applied to adjust the significance level and control for type I error arising from multiple comparisons. All statistical tests will be two-sided, with a P value of less than .05 considered statistically significant. Institute of Basic Research in Clinical Medicine, China Academy of Chinese Medical Sciences will perform all statistical analyses.

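### Randomization is stratified by 13 centers, but no center term is named in the mixed model, the imputation model or the categorical tests; if outcomes differ by center, the analysis is modestly conservative.

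*Protocol*

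**What the plan says.** Section 3 describes a "parallel-group controlled trial that will be conducted at 13 tertiary hospitals in China". Section 3.1 sets the allocation: "A stratified block randomization method will be employed, using study center as stratification factors", and "Random sequences with a block size of 6 will be generated using SAS". Section 5.1 gives the ratio: "Participants will be randomly assigned in a 1:1:1 ratio to one of three treatment groups". Section 14.2 plans 42 patients at one center and 33 at each of the other twelve.

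Section 10.6 specifies the analysis in some detail. For the linear mixed model: "The model will include fixed effects for treatment group, time (modeled as a categorical factor), and their interaction". The prespecified covariates are "sex, age, body mass index, total duration of lumbar disc disease, duration of the current progressive episode, and degree of herniation" at the symptomatic level. The imputation model takes the longitudinal outcomes at all visits plus those same covariates. For categorical outcomes, "between-group comparisons will be performed using the chi-square test or Fisher's exact test as appropriate", with a Bonferroni correction.

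No center term is named in any of these. Section 10.6 does not state the random effects of the mixed model at all, not even the participant term.

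**The concern.** An analysis should reflect the restriction placed on the randomization. Blocks within center make the arms nearly equal at every hospital, so differences in outcome between hospitals largely cancel from the comparison of arms. A model without center does not know this. It treats the between-center variation as ordinary residual (or participant) variation and includes it in the standard error of the difference between arms at a visit. If hospitals do differ, confidence intervals come out wider than they need be, tests run below their nominal level and some power is lost.

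The level of detail in Section 10.6 matters here. It fixes the fixed effects, the covariates, the software packages, the multiplicity method and the contents of the imputation model. On its face, that list omits the one factor on which the randomization was stratified.

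**Working it through.** **Inputs.** From Section 3.2: difference 7 ODI points, SD 15.1, two-sided alpha 0.05, power 90%, Dunnett's test for two comparisons, 113 per group, 133 after 15% dropout, target 146. From Section 14.2: 42 + 12 × 33 = 438 = 3 × 146. Evaluable per arm at the target: 146 × 0.85 = 124.1, taken as 124. Assumed, because the protocol gives no figure: the ICC, the between-center share of the variance in ODI change to week 2 after the listed covariates, at 0, 5, 10 and 15%.

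**The plan's own figure.** With the large-sample Dunnett critical value c = 2.212 and z = 1.282 for 90% power, n = 2 × [15.1 × (2.212 + 1.282) / 7]² = 113.6. The stated 113 gives 89.8% power, so it reproduces within rounding. 113 / 0.85 = 133 also holds. None of this depends on how center is handled.

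**Standard error and test size.** If center variation cancels from the contrast, the true standard error is √(1 − ICC) times the one the model reports.

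- Overstatement = 1/√(1 − ICC) − 1
- Actual size of a nominal 5% test = 2 × [1 − Φ(1.96/√(1 − ICC))]

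| Assumed ICC | SE too large by | Actual size |
|---|---|---|
| 0% | 0% | 5.0% |
| 5% | 2.6% | 4.4% |
| 10% | 5.4% | 3.9% |
| 15% | 8.5% | 3.4% |

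**Power, like for like.** At 124 per arm the reported SE without center is 15.1 × √(2/124) = 1.918, and 7/1.918 = 3.650. Take c = 2.22, the Dunnett value with finite degrees of freedom.

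- Without center, the estimate already has the smaller true spread, but the test uses the larger SE: power = Φ[(3.650 − 2.22)/√(1 − ICC)]
- With center: power = Φ[3.650/√(1 − ICC) − 2.22]

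| Assumed ICC | Without center | With center | Gain |
|---|---|---|---|
| 0% | 92.4% | 92.4% | 0 |
| 5% | 92.9% | 93.6% | 0.7 to 0.8 points |
| 10% | 93.4% | 94.8% | 1.4 points |
| 15% | 94.0% | 95.9% | 1.9 points |

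With all 146 per arm evaluable (c = 2.212) the gain is smaller: 96.4 to 96.8% at ICC 5% and 96.7 to 97.5% at 10%.

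**Simulation check.** Most centers enrol 33, which is not a multiple of the block size of 6, so balance within center is close but not exact. Blocks of 6 were therefore simulated over centers of 42 and 12 × 33, with 4,000 runs per ICC, a single time point and least squares with and without center.

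- ICC 0 and 2%: the two analyses do not differ beyond simulation error.
- ICC 5%: without center the rejection rate was 4.7%; with center, 5.4%.
- ICC 10%: without center the average SE was 1.760 against a true spread of 1.655, rejecting 3.6%; with center, 1.677 against 1.651, rejecting 4.6%.

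Direction and rough size agree with the formulas.

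**The case against.** **The size is assumed.** No between-center ICC appears in the protocol, and at 0 to 2% nothing visible changes. The relevant quantity is also not the center share of ODI itself. The primary outcome in Section 6.1 is change from baseline to week 2, and stable center differences in ODI level cancel in a change. Both points stand. A reader might infer that the standard errors are certainly too large; the documents support this only to the extent that ODI change differs between centers.

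**Center may be in the model after all.** Section 10.6 leaves the random effects unstated, so a center random intercept is not strictly excluded, and a statistical analysis plan (not available for this review) could supply it. This stands as a caveat. What can be said is that no center term is named, although the rest of the specification is detailed.

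**Nothing is invalid.** This is correct. The treatment estimate is not biased, and the error runs toward caution. A reader might infer inflated type I error or a wrong sample size; neither follows.

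**The power gain is easily overstated.** It is tempting to compare every center-adjusted figure with 92.4%. That is the unadjusted power at ICC 0 only. When centers differ, the unadjusted estimate is also less variable, so its power rises too. The like-for-like gains are 0.7 to 1.9 points.

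**LOPM operators.** A reader might count operator skill among the center differences that cancel. It does not cancel: LOPM is given in only two of the three arms (Section 5.1), so operator differences change the effect of the combination against YBT from center to center. A center main effect or random intercept does not remove that heterogeneity.

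**Categorical outcomes.** Disc resorption is secondary, and Section 6.3 has two surgeons make all MRI measurements, so evaluator differences between hospitals are a weak argument there. For sparse adverse events over 13 strata, Fisher's exact test is reasonable.

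**Conclusion.** The mismatch is real: the factor used to stratify the randomization is not among the terms named for the mixed model, the imputation or the categorical tests. Its consequence is conditional and modest. Over an assumed ICC of 0 to 15%, standard errors would be 0 to 8.5% too large and a nominal 5% test would run at 5.0 down to 3.4%. Naming center would gain at most about 1.9 points of power at 124 per arm. These figures assume a common treatment effect across centers, near-balance within center, no center random intercept in the unstated random effects, and an ICC that refers to week-2 ODI change after covariates. The omission itself can be stated with confidence; its size cannot. The correction is worth making because it is nearly free, and because fixing it in advance removes a later choice between results with and without center.

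**What to change.** In Section 10.6:

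- Add study center to the linear mixed model, as a fixed effect or as a random intercept alongside the participant random effect, and state the random effects explicitly.
- Add study center to the imputation model.
- For disc resorption, replace the plain chi-square or Fisher test with a center-stratified comparison, for example a Mantel-Haenszel risk difference, keeping the Bonferroni correction. Sparse adverse events may stay with Fisher's exact test.

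The cost is 13 − 1 = 12 degrees of freedom among 438 participants if center is a fixed effect, plus the wording. No new data are needed, since center is known from the randomization. The change should be made before the analysts see treatment allocation. It does not address variation in the LOPM effect between centers, which would need a separate treatment-by-center analysis.
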